### Recruitment and Consent Procedures

The Cal State LA Institutional Review Board (IRB) will approve all recruitment and consent procedures prior to enrollment begins. All study staff will complete IRB research training through Cal State LA. Recruitment will take place in 2 ways: through referrals from entities that serve young children and through targeted outreach. The primary recruitment site for this project will be Centro de Niños y Padres early intervention program. Additional sites identified for referrals include Federally Qualified Community Health Centers, Family Resource Centers, and the Diagnostic Clinics, all programs that serve children with disabilities from low-resource communities in the Los Angeles area. Presentations on ASD and free screening events will be scheduled for parents and staff at childcare and Early Head Start locations in proximity to the university as well as pediatric practices to facilitate recruitment. Parents of children identified as having elevated concern for ASD will be informed about potential participation in our research study. The referring organization will proceed, as appropriate, with standard referrals (EI, Child Find), regardless of interest in participating in our research study. The partnering organization will provide referral contact information (study flyer) to the project staff for all families that indicate interest and consent to be contacted by the project staff.

Once a telephone or email inquiry or referral from a partnering organization is received, project staff will call the family to explain the purpose and procedures of the study. If the participant indicates interest in participation, project staff schedule an assessment appointment with the family. The potential participant will complete a screening assessment consent form, which will allow the assessor (principal investigator [PI] for English, bilingual research assistant for Spanish) to administer the Modified Checklist for Autism in Toddlers, Revised, with Follow-Up (MCHAT), which is a parent-report screening tool to assess autism risk [27]. If the child scores below 3 on the MCHAT or does not meet all eligibility requirements, the parent will be compensated for the visit (US $25) and receive an assessment report, and all study materials will be destroyed. The assessor will continue with baseline assessments if the child and family meet all eligibility criteria: child is between 16 and 36 months of age, is minimally verbal or pre-verbal, scores 3 or above on the MCHAT, and has no other physical or sensory disabilities.

Before starting baseline assessments, the assessor will review the informed consent form in the appropriate language with the participant, and any questions will be answered. The participant will be told that this is a research study, that his or her participation will not positively or negatively affect the provision of services to the family, and that he or she is free to decline to answer any questions or to cease participation at any point. The confidentiality of the information will be assured. The participant will be told that no identifying information will be retained on any of the data collection forms and that a unique and nonidentifying ID code number will be assigned in lieu of his or her name. The participant will be asked to sign 2 copies of the informed consent (1 for the participant to keep, 1 for the project files), after which baseline assessment will begin. Participants will then receive 6 weekly links to the online

modules in their language of preference as outlined in the following sections.

### Considerations for Families From Low Income and Diverse Communities

Some families, especially from communities of color, may have had negative experiences that result in a lack of trust in the research community. Further, they may perceive research participation as lacking benefit to them and their child. Bonevski and associates [28] outlined strategies to improve trust and participation in low-resource and culturally diverse communities in a systematic review. They highlight a need for increased flexibility in scheduling, the provision of monetary or tangible incentives, reduced travel to the research site, and capitalizing on connections within the community of interest [28]. These recommendations have been incorporated in the development of this study, so that the assessor will schedule appointments with the parent to accommodate their schedule and preferences, participants will receive compensation for their time after each assessment visit, and community-based EI providers and medical practices that accept Medicaid reimbursement will be the main referral points for the study.

Baseline assessments will be conducted with all children and parents prior to participation in the study. The purpose of the screening and baseline assessments is to confirm ASD risk and assess parent, child, and family characteristics prior to their receipt of intervention. In addition, posttest (6 weeks after the start of intervention) and follow-up (6 weeks postintervention) assessments will be conducted to assess changes in parent and child characteristics over time. Parents will receive US $25 for their time for completing screening or baseline, posttest, and follow-up assessments (US $75 total). All time point assessments will involve travel to Cal State LA.

### Enrollment and Participation

Over 1 year, 24 parent/child dyads will participate in the study. The parents will receive 6 weekly emails or text messages, each with an active link to access an online training module. All electronic data will be stored in a password-protected university server, and only IRB-authorized personnel will be granted password access.

### Screening Measures

For autism risk, the MCHAT [27] is a parent-report autism screening tool for children 16 to 30 months of age. It will be collected pre-intervention. Children who score above 3 will qualify to participate in the study and will be referred for a diagnostic evaluation.

### Control Measures

#### Demographic Questionnaire

The demographic questionnaire will be created by investigators. The questionnaire will include questions regarding parent age, education, income, employment, English language proficiency, health status, child age, and gender. It will be collected pre-intervention.

#### Service Use Questionnaire

The service use questionnaire will be created by the PI. Parents will be asked to indicate which services the child is currently receiving, including the number of hours received weekly for each service. Services may include applied behavior analysis therapy, occupational therapy, physiotherapy, speech therapy, recreational or social activities, or education-based services (EI, preschool). Services used and hours of services will be counted for a total score and will be examined individually. This will be collected pre-intervention, postintervention, and at follow-up.

#### Recruitment Site

I will control for recruitment site, as participants recruited from different sites may have had very different experiences related to their child’s development and represent distinct demographic groups. This will be collected pre-intervention.

### Primary Outcome Measures

#### Social Communication

Social communication will be coded from a recorded play session between the parent and child with a standard set of toys using frequency counts to identify the presence of the communicative behavior (vocalizations, eye contact, or positive affect) over a 5-minute video-recorded play session. The overall percentage of intervals in which the children used any type of social communication will be calculated. This will be collected pre-intervention, postintervention, and at follow-up.

#### Parent Fidelity of Implementation

Parent Fidelity of Implementation will be scored using a continuous 1-minute interval recording system over a 10-minute video segment of a recorded play session between the parent and child with a standard set of toys. Parents will be scored for the correct use of each of 5 PRT principles (presenting clear opportunities, child choice, immediate contingent responses, natural reinforcers and reinforcing verbal attempts, and correct verbal responses), and an overall percentage will be calculated. This will be collected pre-intervention, postintervention, and at follow-up.

#### Satisfaction

Parents will complete a survey rating their satisfaction with their training on a 5-point Likert scale. Items will include, but are not limited to, accessibility, helpfulness, convenience, and thoroughness of training program and materials. Space for parent suggestions will also be provided. This will be collected postintervention.

#### Child Development Knowledge

To assess child development knowledge, a researcher-created measure will be used that was developed to assess parent knowledge of typical and atypical development. This will be collected pre-intervention, postintervention, and at follow-up.

### Secondary Outcome Measures

#### Overall Language

The Preschool Language Scales Fifth Edition [29] is a norm-referenced, play-based, comprehensive developmental language assessment for children from birth to age 7 years. This will be collected pre-intervention, postintervention, and at follow-up.

#### Expressive Language

The MacArthur Bates Communicative Development Inventories Words and Gestures Form [30] is a standardized, parent-report form that tracks young children's language and communication skills including words the child understands, words the child uses, and gestures tried or completed. This will be collected pre-intervention, postintervention, and at follow-up.

#### Parent Stress

The Parenting Stress Index-Short Form [31] is a self-report screening tool that helps providers and families identify the sources and different types of stress that come with parenting. The 36 items are divided into 3 domains that combine to form a Total Stress scale: Parental Distress, Parent-Child Dysfunctional Interaction, and Difficult Child. This will be collected pre-intervention, postintervention, and at follow-up.

#### Empowerment

The Family Empowerment Scale [32] is a 24-item self-report measure that evaluates levels of empowerment experienced by parents or other caregivers of children with emotional or behavioral challenges. This will be collected pre-intervention, postintervention, and at follow-up.

#### Challenging Behavior

The Child Behavior Checklist 1.5-5 [33] obtains caregivers’ self-report ratings of 99 problem items. Items are scored on the following scales: Emotionally Reactive, Anxious/Depressed, Somatic Complaints, Withdrawn, Attention Problems, Aggressive Behavior, and Sleep Problems. The assessment also includes open-ended questions to obtain additional qualitative information about child problems and strengths. This will be collected pre-intervention, postintervention, and at follow-up.

#### Social Skills

The Ages & Stages Questionnaire-Social Emotional is a parent-report measure focused on social and emotional development in young children. The Ages & Stages Questionnaire-Social Emotional provides insight into important developmental areas, such as self-regulation, communication, autonomy, compliance, adaptive functioning, affect, and interaction with people. This will be collected pre-intervention, postintervention, and at follow-up.

### Sample Size Determination

A recently published report on a monolingual, brief, online, PRT pilot reported significant improvement in parent fidelity of implementation of PRT strategies and measures of child social communication (vocalizations, eye contact, and positive affect) after 5 weeks, with large effect sizes of 1.80 and 1.12, respectively [20], similar to findings from earlier studies. Therefore, given a conservative estimated effect size of 0.8 for our primary outcomes between baseline and postintervention timepoints, a sample size of 13 is needed to have 80% power to detect a significant difference in primary outcomes between these timepoints given an α of .05. Given our goal of enrolling 24 participant dyads and assuming normal distributions, we can estimate 97% power to detect a significant difference in primary outcomes between baseline and postintervention.

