### Quantitative Analysis

Linear mixed-effects model analysis will be used to explore most parent-reported and coded outcomes because (1) it allows for individual differences in parent responses over time to be included in the model as a random effect so that the variance in responses is partitioned into a time-within-parent component and a between-parent component, (2) using maximum likelihood estimation in a linear mixed-effects model allows for the use of all available data to evaluate the parameter values and is currently considered the state-of-the-art method for handling missing data, and (3) linear mixed-effects models perform well with small samples. The linear mixed-effects models will evaluate time as the main fixed effect using discrete time variables (ie, 2 dummy variables with baseline as the “referent”). Separate regression models will be run for each outcome. Additional variables to be included in each regression model will include total score of other services used, recruitment site, and only demographic variables significantly related to the outcome (given the small sample size).

Cohen d effect sizes will be calculated between time periods and reported for all analyses of interest as a measure of the magnitude of any changes in outcome measures. Mixed models will also be utilized to test if changes from baseline on outcome variables differ by parent language preference for training (Spanish or English) over time. HOLA acceptability will be determined by the average parent rating on the Parent Satisfaction measure. If the average ratings for parent satisfaction items are 3.5 or higher, the training may remain as written. Items with parent satisfaction ratings lower than 3.5 will be explored during Spanish and English focus groups, and individual items will be refined according to feedback. Focus group transcripts will be coded and analyzed thematically to inform continued program improvement.

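### The 13 dyads for 80% power and the 97% power at 24 come from a normal approximation for one complete paired contrast, and cannot apply to every outcome listed as primary

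*Protocol article*

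**What the plan says.** The Sample Size Determination section of the protocol article cites effect sizes of 1.80 for parent fidelity and 1.12 for child social communication from an earlier online pilot. It then sets its own value, "given a conservative estimated effect size of 0.8 for our primary outcomes between baseline and postintervention timepoints". From this, with alpha set at .05, it concludes that "a sample size of 13 is needed to have 80% power to detect a significant difference in primary outcomes between these timepoints". The second figure starts from enrolment, "Given our goal of enrolling 24 participant dyads and assuming normal distributions", and reads "we can estimate 97% power to detect a significant difference in primary outcomes between baseline and postintervention".

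Primary Outcome Measures lists four outcomes: Social Communication, Parent Fidelity of Implementation, Satisfaction and Child Development Knowledge. Three are measured before the intervention, after it and at follow-up. For Satisfaction the text says "This will be collected postintervention", and Quantitative Analysis judges it by mean item rating against 3.5. For the modelled outcomes the same section says "Separate regression models will be run for each outcome".

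**The concern.** A sample-size paragraph should let the reader see which test, which outcomes and how many completers the power refers to. Here one effect size, one alpha and one power figure are attached to the primary outcomes as a group. Three things do not fit:

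- At 13 to 24 pairs the normal approximation is optimistic, and at 13 the error is material.
- The power is computed on dyads enrolled, although every assessment requires travel to campus and the posttest follows six weekly modules.
- One of the four primaries has no baseline, so it has no change to detect. Another is a researcher-created measure for which the paragraph cites no effect size.

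At stake is whether the stated power can be taken at face value. A reader could believe that 13 completers would be enough, or that all four primaries are covered at 97%.

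**Working it through.** **Inputs.** From Sample Size Determination: effect size d = 0.8, alpha .05, n = 13 for 80% power, and 97% power at n = 24. From Primary Outcome Measures: four primaries, three with a baseline. Assumptions made here: a two-sided test (sidedness is not stated); d equals mean change divided by the SD of change (the standardiser is not defined, but this reading reproduces the stated figures); and the loss levels, since no rate is given.

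**1. Reproducing the stated figures (normal approximation, one paired contrast).**
- n = ((1.960 + 0.842) / 0.8)² = 12.26, rounded up to 13. This matches.
- Power at 24 = Φ(0.8 × √24 − 1.960) = Φ(3.919 − 1.960) = Φ(1.959) = 97.5%. This matches the stated 97%.
- Alternatives do not fit: the one-sided normal approximation gives 10 and 98.8%, and a two-sample formula gives 25 per arm.

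**2. The same contrast with the paired t.** Power = P(|T| > t(.975, n − 1)), where T is noncentral t with n − 1 degrees of freedom and noncentrality 0.8√n.

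| Dyads with both assessments | Normal approximation | Paired t |
|---|---|---|
| 13 | 82.2% | 75.4% |
| 14 | 84.9% | 79.0% |
| 15 | 87.3% | 82.1% |
| 24 | 97.5% | 96.3% |

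So 80% power needs 15, not 13. At 24 the difference is about one point.

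**3. Incomplete dyads (assumed loss, paired t, alpha .05).**
- 21 completers (3/24 = 12.5% lost): 93.6%
- 19 completers (5/24 = 20.8% lost): 90.9%
- 17 completers (7/24 = 29.2% lost): 87.2%

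**4. Which primaries the figure can cover.**

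| Primary outcome | Baseline measured | Effect size cited |
|---|---|---|
| Parent Fidelity of Implementation | yes | 1.80 |
| Social Communication | yes | 1.12 |
| Child Development Knowledge | yes | none |
| Satisfaction | no | none |

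A baseline-to-postintervention difference exists for three of the four, and the cited evidence supports two.

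**5. Illustration only: three posttest contrasts.**
- Unadjusted at .05, the family-wise error is 1 − 0.95³ = 14.3% if the outcomes are independent, and about 13% by simulation if they correlate at 0.5.
- The probability that all three are significant with 24 completers is 89% if independent (0.963³ = 0.893) and about 91% at correlation 0.5.
- Holm across the three leaves about 95–96% power per outcome at 24 when all three have the assumed effect, a cost of roughly 1–2 points. At the strictest step (.05/3), power is 89.9%.

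**6. Sensitivity to the standardiser.** If 0.8 is in raw-score SD units, the effect on change is 0.8/√(2(1 − r)), where r is the pre-post correlation. Paired-t power at 24 is then 96.3% at r = 0.5, 88.7% at r = 0.3 and 75.6% at r = 0.

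**The case against.** The case for leaving the text alone is substantial. The 97% is not an arithmetic slip: the paired t gives 96.3%. The 13 is not the planned sample, and 24 enrolled against 15 needed allows 9/24 = 37.5% loss before per-outcome power falls below 80%. Mixed models are announced for most outcomes, not all, and Satisfaction already has its own 3.5 criterion, so it is in practice analysed as an acceptability measure. All of this stands, and it limits the seriousness of the point. It does not rescue the 13, nor a power claim worded for primary outcomes that include one without a baseline. Maximum likelihood uses all available data but does not restore lost baseline-to-posttest pairs.

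A reader might go further and infer that the design fails to deliver its stated power for the primaries jointly, or that it has an uncontrolled family-wise error. The documents do not support either. With one effect size, one alpha and separate models, 97% reads naturally as power per outcome. Nothing in the article requires all primaries to succeed. The models are described as exploratory in a single-group pilot, and a multiplicity rule may stand in an analysis plan that is not shown. Nor does the article say that the later trial application will rest on the power figure; it says that the pilot's results will be used.

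**Conclusion.** The point holds as a should-fix. The stated 13 for 80% power is too low by two dyads under the paired t (75% at 13). The 97% is about one point high with no loss and about 3, 6 and 10 points high with 21, 19 and 17 completers. The claim cannot apply to Satisfaction and has no cited effect size behind it for Child Development Knowledge. These results assume a two-sided .05 test, normally distributed changes, and 0.8 measured against the SD of change; the loss levels are assumptions. Under them, 24 dyads remain adequate for each outcome taken singly, so the defect is in the claim and not in the sample size. The family-wise and all-three figures show what a success rule would involve and are not evidence of an error.

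**What to change.** In Sample Size Determination:
- state 15 dyads for 80% power and 96% per outcome with 24 completers, by the paired t, and say that 0.8 is relative to the SD of change;
- give per-outcome power for a stated range of loss, for example 94%, 91% and 87% with 21, 19 and 17 completers;
- limit the claim to the three primaries with a baseline, and say that 0.8 is an assumption for Child Development Knowledge.

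In Primary Outcome Measures, reclassify Satisfaction as a descriptive acceptability measure, which matches how Quantitative Analysis already treats it.

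A cheap further improvement is to name one primary posttest contrast, or to apply Holm to the three posttest-versus-baseline contrasts and quote the power under that rule.

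The required changes are wording only, with no added dyads or assessments, and the stated power becomes slightly less favourable. Holm, if adopted, costs about 1–2 points per outcome at 24 completers when all three outcomes have the assumed effect.

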### Quantitative Analysis

Linear mixed-effects model analysis will be used to explore most parent-reported and coded outcomes because (1) it allows for individual differences in parent responses over time to be included in the model as a random effect so that the variance in responses is partitioned into a time-within-parent component and a between-parent component, (2) using maximum likelihood estimation in a linear mixed-effects model allows for the use of all available data to evaluate the parameter values and is currently considered the state-of-the-art method for handling missing data, and (3) linear mixed-effects models perform well with small samples. The linear mixed-effects models will evaluate time as the main fixed effect using discrete time variables (ie, 2 dummy variables with baseline as the “referent”). Separate regression models will be run for each outcome. Additional variables to be included in each regression model will include total score of other services used, recruitment site, and only demographic variables significantly related to the outcome (given the small sample size).

Cohen d effect sizes will be calculated between time periods and reported for all analyses of interest as a measure of the magnitude of any changes in outcome measures. Mixed models will also be utilized to test if changes from baseline on outcome variables differ by parent language preference for training (Spanish or English) over time. HOLA acceptability will be determined by the average parent rating on the Parent Satisfaction measure. If the average ratings for parent satisfaction items are 3.5 or higher, the training may remain as written. Items with parent satisfaction ratings lower than 3.5 will be explored during Spanish and English focus groups, and individual items will be refined according to feedback. Focus group transcripts will be coded and analyzed thematically to inform continued program improvement.

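### Uncorrected maximum likelihood with 24 dyads makes standard errors slightly too small; REML with small-sample degrees of freedom keeps the missing-data rationale and removes most of the error

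*Protocol article*

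**What the plan says.** The Quantitative Analysis section gives three numbered reasons for using linear mixed-effects models.

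- The first is that "the variance in responses is partitioned into a time-within-parent component and a between-parent component", which reads as a random intercept per parent.
- The second names the estimator: "using maximum likelihood estimation in a linear mixed-effects model allows for the use of all available data to evaluate the parameter values". It adds a remark on the handling of missing data.
- The third is that "linear mixed-effects models perform well with small samples".

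Time enters as two dummy variables against baseline, with a separate model for each outcome. Other services used, recruitment site and selected demographics are added as covariates. The same type of model tests whether change from baseline differs between parents trained in Spanish and in English.

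The section names neither REML nor a degrees-of-freedom method. It does not say whether tests use a z, t or likelihood-ratio reference. The Sample Size Determination section plans for 24 dyads.

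**The concern.** ML estimates variances without allowing for the fixed effects that were estimated from the same data. In a large trial this does not matter. With 24 dyads and three visits the variances come out low, so standard errors are too small, intervals too narrow, and tests reject slightly more often than 5%. A blanket assurance about small samples hides this.

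The reason given for ML does not favour it over REML. REML is also likelihood-based and uses every observed visit.

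Two inferences are affected: the changes from baseline, and the language comparison, where the authors predict no difference. For the latter, a test that rejects too often and an interval that is too narrow both bear directly on the stated prediction. Because each outcome has its own model, the same small bias recurs throughout.

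**Working it through.** **Inputs.** From the article: 24 dyads, three visits, effect size 0.8, α = .05, ML estimation, and a between-parent and a within-parent variance component. Assumed: two-sided tests; balanced data for the closed form; a z or t reference, shown both ways.

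**The plan's own figures.** The article says that "a sample size of 13 is needed to have 80% power to detect a significant difference in primary outcomes between these timepoints". For a paired comparison with the normal approximation:

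- n = ((1.96 + 0.842)/0.8)² = 12.3, rounded up to 13.
- Power at 24 = Φ(0.8 × √24 − 1.96) = Φ(1.96) = 97.5%, against the stated 97%.

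An exact paired t calculation gives 75.4% power at 13, 15 dyads for 80%, and 96.3% power at 24. The stated figures reproduce within tolerance, and two-sided 5% is the reading that produces them. The article states no type I error or standard error for the mixed models, so those are computed below.

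**Closed form (balanced, random intercept).** The within-parent variance under ML uses the divisor n × (3 − 1) = 24 × 2 = 48. The degrees of freedom actually available are:

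- time contrast: 2 × (24 − 1) = 46
- language-by-time: 2 × (24 − 2) = 44

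The ratio of the ML to the REML standard error is √(df/48). True type I error is 2 × P(t_df > c × √(df/48)), where c is the critical value in use.

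| | Time contrast | Language-by-time |
|---|---|---|
| SE ratio | √(46/48) = 0.979 (2.1% too small) | √(44/48) = 0.957 (4.3% too small) |
| ML, t reference | c = 2.013; 2P(t₄₆ > 1.971) = 5.5% | c = 2.015; 2P(t₄₄ > 1.930) = 6.0% |
| ML, z reference | c = 1.96; 2P(t₄₆ > 1.919) = 6.1% | c = 1.96; 2P(t₄₄ > 1.877) = 6.7% |
| REML, z reference | 2P(t₄₆ > 1.96) = 5.6% | 2P(t₄₄ > 1.96) = 5.6% |

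For the time contrast, about half of the excess under ML with z comes from the z reference and about half from ML.

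If the covariance were unstructured instead, the time contrast would have 23 degrees of freedom, and ML would give 6.7% with z and 5.5% with t.

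**Simulation (15,000 runs per case).** Assumptions, none of them from the article: intraclass correlation 0.5, equal language groups, and, where covariates are included, four sites, a services score and two demographic covariates. The Monte Carlo standard error at a rate of 6% is √(0.06 × 0.94/15,000) = 0.2 points.

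| Case, n = 24 | ML, z | ML, t | REML, z | REML, t |
|---|---|---|---|---|
| Time, no covariates, complete | 6.3% | 5.6% | 5.7% | 5.0% |
| Time, covariates, complete | 6.3% | 5.7% | 5.7% | 5.1% |
| Time, covariates, 20% dropout | 7.0% | 6.1% | 6.0% | 5.1% |
| Language-by-time, covariates, 20% dropout | 7.2% | 6.4% | 5.7% | 4.9% |

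The first row agrees with the closed form. In the last two rows the ML standard errors are 3.3% and 5.6% below those from REML. REML with a t reference is close to 5% in every case.

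**The case against.** The strongest reply is that this is a condensed article, that ML appears only in a clause about incomplete data and not as a choice against REML, and that test details belong in an analysis plan that is not shown. Part of this stands: the absence of a degrees-of-freedom method is no finding. But the estimator is named and a small-sample assurance is given, so those two statements can be judged as written.

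A second reply is that the size is small and the stakes are low. This also stands. The study is a single-group pilot whose models explore outcomes, effect sizes are reported throughout, and the one numerical decision rule, a satisfaction rating of 3.5, uses no p value. At the assumed effect of 0.8 with about 97% power, a 2% change in a standard error is unlikely to alter the main result.

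A reader might also infer more than the article supports:

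- **That ML was chosen because mixed models suit small samples.** The two statements are separate. ML is tied to use of all data, and the small-sample remark concerns mixed models in general.
- **That the tests use large-sample critical values.** No reference distribution is stated, so the z figures are conditional.
- **That the error on the time effect grows with every site or demographic term.** Such terms are constant within a parent. In complete balanced data they do not enter the time-contrast calculation, and the simulated rate with them was the same 6.3%.
- **That covariates are picked using over-optimistic ML p values.** The article does not say which model is used for that screen.
- **That coefficients of between-parent covariates are badly affected.** Their number is not given, and no stated hypothesis concerns them.

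**Conclusion.** The point holds in a limited form. The article names ML for models on 24 dyads and adds a small-sample assurance that is true only with suitable corrections. ML by itself, with a correct t reference, takes a nominal 5% test to about 5.5% for a time contrast and 6.0% for language-by-time. If the software applies a z reference, the rates are 6.1% and 6.7%, or about 7% for both under the simulated covariates and 20% dropout. These figures rest on a random intercept and normal data. The closed form also needs balance, and the simulation needs the assumed correlation, covariates and dropout. The consequence is minor: the design and the main conclusions are not threatened. The change is still worth making, because nothing the authors want from ML is lost by it.

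**What to change.** In the Quantitative Analysis section, state that the mixed models will be estimated by REML, with Kenward-Roger or Satterthwaite degrees of freedom for tests and intervals on fixed effects. The second reason can stay almost as it is, since REML uses all available data equally.

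Qualify the third reason rather than delete it: mixed models can be used with a sample of this size, provided that REML and small-sample degrees of freedom are applied.

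The cost is a software option, one sentence and slightly wider intervals. Under the closed form, the standard error rises by a factor of 1/0.979 = 1.02 for time and 1/0.957 = 1.04 for language-by-time. If the default was a z reference, the critical value also rises from 1.96 to about 2.01 for time and 2.02 for language-by-time.
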